Equi-analgesia or equi-efficacy among the treatment groups is an essential part of the study as it is the primary end-point of analgesic treatment during labor. The definition of equi-analgesia in our study is a difference in pain appreciation (VAS score) among the two study groups of 10% or less. Preliminary data in perioperative patients on PCA opioid treatment ([name], oral communication) indicate that at VAS scores ranging from 4 to 8 (the expected range in our study), changes (i.e. increases) in pain score of 10% or larger will prompt an action of the patient (i.e. she will require additional pain relief by pressing the PCA button). Extrapolating these data to the current study suggests that at VAS score differences of 10% or greater clinical differences in pain appreciation may be assumed.

It is expected that economical evaluation of both strategies will show a significant reduction in costs of this innovative strategy.

Other outcome measures are pain scores, patient satisfaction, maternal and neonatal outcome and validated questionnaires.

This study considering cost effectiveness of RPCA as first choice analgesia versus EA could strongly improve the care for 180.000 women, giving birth in the Netherlands yearly (according to LVR data (2008) 30% of pregnant women under care in a hospital need pain relief during labor), by giving them access to pain relief during labor if needed, 24 hours a day.

In the guidelines of gynecologist and midwives it is recommended to discuss the opportunities of pain relief during labor antenatal (1).

An estimation of costs for RPCA versus EA shows a decrease of 64 euro per patient. The difference in costs is due to the extra costs of anesthetic staff and nurses, required when EA is given. Nationwide this could potentially save 1.2-4.6 million euro per year, depending on the percentage of women needing pain relief, varying respectively from 10-40%.

The results of the study will provide insight on whether RPCA in women in labor will reduce costs as compared to EA, assuming RPCA is equivalent to EA with respect to pain appreciation scores. At present, no clinical study has been published or undertaken to investigate this issue.

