## Sample size calculation

The initial analysis will be performed by intention to treat. We hypothesize that there is no difference in pain appreciation scores with the two sided test, an alpha of 0.05 and 90% power. In this equivalence design in each group 102 women have to be treated to exclude a potential clinical relevant difference of 10% (10 point scale, estimated SD 2.2). Allowing for 10% and 30 % cross-over/ non-compliance in the control group and experimental group respectively, 568 patients are required. When only 50 percent of all women need actually treatment 1136 women have to be randomized. We estimate that in the group of pregnant women who are willing to participate in the study 50% will actually need pain relief. This in contrast to the general Dutch pregnant population, which is known for a low uptake of pain relief during labor.

**4.4.1** Sample size for population of low risk pregnant women.

We hypothesize that there is no difference in pain appreciation scores with the two sided test, an alpha of 0.05 and 90% power. In this equivalence design in each group 102 women have to be treated to exclude a potential clinical relevant difference of 10% (10 point scale, estimated SD 2.2).

We estimate that in the group of pregnant women who are willing to participate in the study 50% actually need pain relief. Therefore 408 women have to be randomized.

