## Summary of findings from clinical and non-clinical studies

Remifentanil, is a new synthetic opioid (anilidopiperidine) with direct agonist action specifically on mu-opioid receptors (7). The rapid onset and offset of the drug make remifentanil very suitable for administration via patient controlled analgesia (PCA).

Remifentanil is used as an analgesic agent for use during induction and/or maintenance of general anesthesia. It is also used as PCA in postoperative patients. Indications, contra-indications, farmacodynamic properties and possible side effects are described in the SmPC (Summery of Product Characteristics) of remifentanil/ Ultiva®(24).

Remifentanil PCA can be used for analgesia during labor. Placental transfer of remifentanil does occur but appears to be rapidly metabolized, redistributed, or both. There were no adverse neonatal or maternal effects, only mild maternal sedation and respiratory changes (8). There have been multiple clinical studies on the use of remifentanil in the parturient (9-21). In our unpublished data (pilot study and STER study), 100 women received RPCA and only in one case medication had to be stopped because of serious side-effects (decrease in respiratory rate).

In epidural analgesia low concentration of local anesthetic (ropivacaine) with opiates (sufentanil) is administered via continuous infusion in the epidural space. Reported maternal complications include hypotension, itching, drowsiness and fever. Also accidental punctuation of the dura which can result in post-dural headache. Epidural analgesia can also influence the course of labor (2).

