  23. Apgar 1 and 5 minutes: continuous, quantitative
  24. Arterial umbilical cord pH: continuous, quantitative
  25. Admission to neonatal ward: categorical, quantitative (yes/no)
  26. Number of visits to/from primary health care mother: continuous, quantitative
  27. Number of visits to/from primary health care child: continuous, quantitative
  28. Number of visits to/from gynecologist: continuous, quantitative
  29. Number of visits to/from pediatrician: continuous, quantitative
  30. Duration of neonatal admission: continuous, quantitative

Duration of maternal admission: continuous, quantitative

We will report on the primary outcome measure, pain appreciation, as area under the pain appreciation curve (AUC), this as a measure for the aggregate effect of pain appreciation over a period of time (27). Total pain relief (TOTPAR) is a time weighted measure of AUC or total area under the pain appreciation curve and is a summary measure that integrates serial assessments of a subject’s pain appreciation over the duration of the study. The AUC will be analyzed from the start of active labor and for the whole duration of labor. We will also perform analysis from start of pain relief for the duration the pain relief is given. Subgroup analysis is planned for the AUC for 0-4 hours, 4-8 hours and >8 hours after the start of pain relief.

The trial is designed as an equivalence trial in which the null hypothesis

is that the difference in pain appreciation score between the two treatment groups is

greater than 10%. Preliminary data in perioperative patients on PCA opioid treatment show that changes (i.e. increases) in pain score of 10% or larger will prompt an action of the patient (i.e. she will require additional pain relief by pressing the PCA button). Extrapolating these data to the current study suggests that at VAS score differences of 10% or greater clinical differences in pain appreciation may be assumed.

The analysis of the randomised clinical trial will be by intention to treat, stratified for

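### The post-relief AUC windows use an area with no stated division by time, and entry to the later windows is decided after randomisation

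*Protocol*

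**What the plan says.** Section 8.1 reports the primary outcome, pain appreciation, as an area under the curve over several periods. For the main period: "The AUC will be analyzed from the start of active labor and for the whole duration of labor". For a second: "We will also perform analysis from start of pain relief for the duration the pain relief is given". Then come the windows: "Subgroup analysis is planned for the AUC for 0-4 hours, 4-8 hours and >8 hours after the start of pain relief".

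On the scale of the measure, the same section says: "Total pain relief (TOTPAR) is a time weighted measure of AUC or total area under the pain appreciation curve". It presents the AUC as an aggregate over a period and states no division by observed time. For pain scores it lists the area under the curve and the mean score as two separate summaries.

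The margin is set on the score itself. In section 1, equi-analgesia "is a difference in pain appreciation (VAS score) among the two study groups of 10% or less". In section 4.4 the aim is to "exclude a potential clinical relevant difference of 10% (10 point scale, estimated SD 2.2"). No margin, test or decision rule is attached to the windows.

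Section 5.2 states: "Epidural analgesia can also influence the course of labor (2"). It gives neither direction nor size, and the protocol gives no expected duration of labour or of pain relief.

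**The concern.** A subgroup is normally fixed at baseline. Whether a woman contributes to 4-8 h or >8 h depends on how long she stays on relief, which is known only after randomisation and which the protocol accepts may depend on treatment. The women compared in a late window are therefore a different selection in each arm.

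Separately, a total area is score multiplied by time. Section 6.1.1 makes a high score mean high satisfaction, so the arm with longer relief gains area and looks more satisfactory without any woman being more satisfied.

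These windows are the only planned look at how satisfaction develops with hours on each method. If section 8.1 is followed as worded, a fall-off over time could be produced or hidden by duration alone. The same scaling issue reaches the whole-labour AUC, which is the primary outcome.

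**Working it through.** **Scale of the margin.** Inputs from section 4.4: "two sided test, an alpha of 0.05 and 90% power", SD 2.2, and 10% of a 10-point scale = 1 point. Women per group = 2 × (1.960 + 1.282)² × 2.2² / 1² = 101.7, so 102, the protocol's figure. The margin behind the sample size is thus 1 point of score, not a percentage of an area.

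**No distribution needed.** Constant score 6 in both arms, labour of 8 h in one and 9 h in the other. Total areas are 6 × 8 = 48 and 6 × 9 = 54, a 12.5% difference. Divided by time, both are 6.

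**Assumptions for the windows** (none is in the protocol):
- Mean score 6 in both arms, with SD 2.2 from section 4.4.
- Time on relief D is lognormal with log-SD 0.6. The median m is 5 h in one arm and 5.5 h or 6 h in the other (10% or 20% longer).
- Correlation between score and log-duration is 0 or -0.3.
- Only women who enter a window are counted in it.

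**Problem 1: undivided area.** Let S(t) = 1 - Φ((ln t - ln m)/0.6). Mean hours in a window among entrants are ∫₄⁸S(t)dt / S(4) and ∫₈^∞S(t)dt / S(8). With correlation 0 the mean area is 6 times these hours.

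| | m = 5 h | m = 5.5 h | m = 6 h |
|---|---|---|---|
| Share reaching 4 h | 64.5% | 70.2% | 75.0% |
| Share reaching 8 h | 21.7% | 26.6% | 31.6% |
| Mean hours, 4-8 h | 2.467 | 2.602 | 2.727 |
| Area, 4-8 h | 14.80 | 15.61 (+5.5%) | 16.36 (+10.5%) |
| Mean hours, >8 h | 3.802 | 4.128 | 4.464 |
| Area, >8 h | 22.81 | 24.77 (+8.6%) | 26.79 (+17.4%) |

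With correlation -0.3, simulation gives about +7% and +13% for 4-8 h, and about +10% and +20% for >8 h. With equal durations the ratio is 1.00 in every window.

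The 0-4 h window, which every treated woman enters, also drifts slightly if left undivided: mean hours are 3.571, 3.659 and 3.727, or +2.5% and +4.4%.

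For the whole-labour AUC at equal scores the area is proportional to duration. A period 10% or 20% longer gives +10% or +20%.

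**Problem 2: selection alone.** The mean score among women reaching t hours is 6 + 2.2 × ρ × λ(a), where a = (ln t - ln m)/0.6 and λ(a) = φ(a)/(1 - Φ(a)). With ρ = 0 the shift is 0. With ρ = -0.3, 2.2 × 0.3 = 0.66:

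| | m = 5 h | m = 5.5 h | m = 6 h |
|---|---|---|---|
| Beyond 4 h: λ | 0.577 | 0.494 | 0.423 |
| Mean score | 5.62 | 5.67 (+0.05) | 5.72 (+0.10) |
| Beyond 8 h: λ | 1.354 | 1.233 | 1.126 |
| Mean score | 5.11 | 5.19 (+0.08) | 5.26 (+0.15) |

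Under much harsher assumptions (duration ratio 1.5, correlation -0.7) the shift beyond 8 h is 0.76 points, still below 1.

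**After division by observed time.** Identical constant scores give a 0% difference in every window and over whole labour, whatever the durations. The selection shift of problem 2 remains.

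**The case against.** The strongest reply is that the text is open rather than wrong. A time-weighted measure may mean a time-averaged score, which removes problem 1 altogether. Section 8.1 does not say who enters a window or how women who have delivered are counted, and such detail is commonly left to a statistical analysis plan. The windows are subgroup analyses without a margin or a claim. Duration of analgesia is recorded and time to delivery is analysed by Kaplan-Meier, so unequal exposure would be visible. Every duration used above is assumed.

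Much of this stands and limits the point. It does not remove it. The protocol itself fixes the windows, calls them subgroups and describes the measure as a total area. Listing the area and the mean as separate summaries for pain scores suggests that the authors do not treat an AUC as a mean. If the wording is only ambiguous, one of its readings still builds duration into the outcome.

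A reader might infer that restricting the late windows to women still in labour is what pushes the difference past the 10% margin. The documents do not support that. Selection on its own creates no difference when score and duration are unrelated, and a small one under the correlation assumed here; almost all of the area difference comes from not dividing by time. Nor is 10% a threshold for these windows. The margin is 1 point, which is 1/6 = 16.7% of a mean of 6. On that yardstick the 4-8 h figures fall inside, and only >8 h at 20% longer passes, barely at correlation 0.

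A reader might also infer that EA is expected to lengthen labour. The protocol says only that it can influence its course.

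**Conclusion.** The point holds as two separate, modest defects in section 8.1. An undivided area lets unequal time on relief appear as a difference in satisfaction: about 5% to 7% (4-8 h) and 9% to 10% (>8 h) if one arm lasts 10% longer, and 11% to 13% and 17% to 20% if it lasts 20% longer. The whole-labour AUC is affected in the same way, by 10% and 20%. Independently of scaling, the 4-8 h and >8 h windows do not compare the randomised groups, but the shift in mean score is only 0 to about 0.15 points here.

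These sizes rest on the assumed lognormal durations, the assumed correlation and the total-area reading. They show sensitivity to duration; they do not predict this trial's result or show a breach of a stated limit. This is a clarification worth making, not a fault that undermines the trial.

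**What to change.** In section 8.1, define each AUC, for whole labour, for time on relief and for every window, as the area divided by the time that the woman was observed in that period. The result is a time-weighted mean on the scoring scale, the scale on which the margin is set.

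Report 4-8 h and >8 h descriptively, with the number of women contributing per arm, and make no equivalence or difference claim for them. Division by time does not cure the selection, which is why the descriptive label is needed as well. A repeated-measures model of all scores is an optional addition.

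The cost is a change of wording; the serial scores and the duration of analgesia are already collected. The downside is less simple late-window tables and no formal claim about late hours.

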### Secondary study parameters/endpoints

If RPCA is equivalent to EA with respect to pain appreciation the next endpoint will be the costs of both interventions. For both strategies the cost of perinatal care for mother and child, starting at the onset of labor and ending ten days after delivery, will be registered and compared (without discounting). The costs consist of costs of delivery/childbirth (course and mode of delivery), postnatal maternal care (hospitalization, outpatient visits), neonatal care (admission to NICU/neonatology ward, outpatient visits) and primary care (midwife, general practitioner, maternity care).

Maternal outcome

- Morbidity (post spinal headache, postpartum haemorrhage (>1 litre or administration of blood products), uterine rupture, eclampsia, amniotic fluid embolism, myocardial infarction, admission to ICU, other (defined as major maternal morbidity by local researchers).
- Maternal mortality
- Prolonged maternal admission. Admission in days measured from delivery of the child.
- Diagnosis during admission: endometritis, suspected infection, UTI treated with antibiotics, wound infection treated with antibiotics, obstructed bowel disease, pneumonia, trombo-embolic complications, hypertensive disorders, postpartum haemorrhage, post caesarean, pre-eclampisa/HELLP, admission due to condition child, other.

Maternal parameters

- pain scores, measured hourly from start of labor using a VAS scale
- pain appreciation scores, measured hourly from the start of labor and after start of pain relief every 15 min in the first hour and hourly after that on a VAS scale.
- satisfaction with pain, measured on a scale of 0-10 after delivery
- side effects, during administration of pain relief
  - hypotension (systolic blood pressure <90 mmHg of <25% below baseline)
  - nausea/vomiting (none, mild, moderate, severe)
  - itching (none, mild, moderate, severe)
  - respiratory depression (respiratory rate <8/min)maternal fever during labor (temperature >38°C)

Neonatal outcome

- Apgar scores ≤ 6 after 1 and 5 minutes
- Umbilical cord pH < 7.10
- Admissions to the neonatal ward

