## Study procedures

Women will be asked to participate in this study before active labor has started, preferably during antenatal consult in the third trimester. They will be randomized and allocated to one of the treatment groups. If they request pain relief during labor they will be treated according to randomization with:

1. Remifentanil patient controlled analgesia; 30 microgram boluses, lockout time 3 minutes, maximum dose limit 1200 microgram/hour. Possibility of increasing or decreasing the bolus dose. When indicated EA is available.

2. Epidural analgesia; according to local protocol. When indicated RPCA is available.

There will be no additional invasive tests performed. Maternal vital parameters (temperature, heart rate, blood pressure, respiratory rate and pulse oxymetry) will be monitored non invasively at regular intervals. In the first hour after starting pain relief these parameters will be monitored with intervals of no longer than 15 minutes, after that with intervals of no longer than 1 hour. Maternal pulse oxymetry will also be monitored continuously.

Fetal heart rate and uterine activity will be measured continuously by external monitoring. When data are difficult to interpret or complications (such as meconium stained amniotic fluid, failure to progress in labor) occur, invasive monitoring by means of scalp electrode and intra-uterine pressure recording can be instituted.

Observations for known side effects will be made; respiratory depression, hypotension, nausea/vomiting and itching. Side effects will be managed by established local protocols.

Hypotension (systolic blood pressure < 90 mmHg or > 25% below baseline) will be treated with intravenous fluids, ephedrine 5 mg i.v. or phenylephrine 0.1 mg i.v. When oxygen saturation drops below 92% oxygen will be given.

Maternal pain score and pain appreciation score will be assessed using a visual analogue scale (VAS) ranging from 0-10. Women will be asked to mark the level of pain experienced during a contraction every hour starting at admission in the delivery room. Pain appreciation scores will be asked every hour, participating women will be asked to mark their level of satisfaction with analgesia. This will also be assessed using the visual analogue scale ranging from 0-10. After delivery an overall satisfaction score with pain(0-10) will be asked. Patient satisfaction will also be assessed by HADS and WDQ.

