# STATISTICAL ANALYSIS

## Descriptive statistics

- 1. Maternal age: continuous, quantitative
  2. ASA physical status: continuous, quantative (1-5)
  3. Body Mass Index: continuous, quantative
  4. Parity: categorical, quantitative: (nulliparous / multiparous)
  5. Previous cesarean delivery: categorical, quantitative (yes/no)
  6. Gestational age: continuous, quantitative
  7. Maternal origin: categorical, quantitative (Caucasian, Mediterranean, Creole, Asian)
  8. Educational level: categorical, quantitative
  9. Number of fetuses: categorical, quantitative (1-3)
  10. Fetal condition at time of request pain relief: categorical, quantitative (optimal, non reassuring, fetal tachycardia)
  11. Start of labor: categorical, quantitative (spontaneous/induction)
  12. Use of oxytocin: categorical, quantitative (yes/no)

Mode of delivery: categorical, quantitative (vaginal delivery, instrumental delivery,

cesarean section)

- 1. Indication for cesarean section/ instrumental delivery: categorical, quantitative Duration first stage of labor: continuous, quantitative
  2. Duration second stage of labor: continuous, quantitative
  3. Time from request to start of analgesia: continuous, quantitative
  4. Duration of analgesia: continuous, quantitative
  5. Conversion from epidural analgesia to RPCA: categorical, quantitative (yes/no)
  6. Conversion from RPCA to epidural analgesia: categorical, quantitative (yes/no)
  7. Type of medication used for epidural analgesia: categorical, quantitative
  8. Increases or decreases in bolus dose for RPCA: categorical, quantitative
  9. Maternal pain scores: continuous, quantitative (0-10)
  10. Maternal pain appreciation scores: continuous, quantitative (0-10)
  11. Maternal satisfaction with analgesia: continuous, quantitative (0-10)
  12. Maternal temperature: continuous, quantitative
  13. Start of intravenous broad spectrum antibiotics; quantitative (yes/no)
  14. Maternal saturation: continuous, quantitative
  15. Maternal respiratory depression: categorical, quantitative (yes/no)
  16. Oxygen administered: categorical, quantitative (yes/no)
  17. Maternal hypotension: categorical, quantitative (yes/no)
  18. Nausea/vomiting: categorical, quantitative (mild, moderate, severe)
  19. Itching: categorical, quantitative (mild, moderate, severe)
  20. Postpartum hemorrhage >1000 ml: categorical, quantitative (yes/no)
  21. Major maternal complication
  22. Post spinal headache: categorical, quantitative (yes/no)

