centre and parity. First, the epidural and remifentanil group will be compared. Relative risks and 95% confidence intervals will be calculated for the relevant outcome measures. Categorical variables will be tested with the Chi-square test or Fisher’s exact test. Continuous variables will be tested with the Mann-Whitney U test. Time to delivery will be assessed using Kaplan-Meier analysis. Pain scores will be analyzed separately. We will report on pain during labor (area under the curve and mean pain score), worst pain during labor, pain scores at request pain relief. The analysis will be repeated on a par protocol basis. Subsequently, planned subgroup analysis will be done for nulliparous versus parous women, previous caesarean section, preterm labor (32 to 34 weeks and 34-37 weeks) and term labor (37-42 weeks), spontaneous versus induced labor, maternal educational level, maternal age (under 35 years versus over 35 years), multiple pregnancy. We will then use decision analysis to evaluate which intervention strategy, ie epidural analgesia or remifentanil is preferred in women who need analgesia during labor.

The low risk women will be included and analyzed in a separate trial. In the Dutch system with midwifery care and home births, there might be a difference in expectation of women with regard to pain during labor.

To be able to convince both primary and secondary care providers, these groups will be analyzed separately.

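### Maternal side effects are analysed only by allocated arm (with an undefined per-protocol repeat), so no analysis gives harm rates by the drug received; add one beside intention to treat

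*Protocol*

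**What the plan says.** Section 8.1 sets one rule for the trial: "The analysis of the randomised clinical trial will be by intention to treat, stratified for" centre and parity. It continues: "Relative risks and 95% confidence intervals will be calculated for the relevant outcome measures". It then adds: "The analysis will be repeated on a par protocol basis". The per-protocol population is not defined, and no other analysis population is named.

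Maternal side effects are a secondary objective (section 2). Section 6.1.2 ties them to exposure: "side effects, during administration of pain relief".

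Section 6.3 makes each arm's fallback the other arm's method. For the control arm it reads: "Epidural analgesia; according to local protocol. When indicated RPCA is available". The RPCA arm has the mirror-image provision.

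Section 4.4 quantifies departures from allocation: "Allowing for 10% and 30 % cross-over/ non-compliance in the control group and experimental group respectively, 568 patients are required". On uptake it says: "When only 50 percent of all women need actually treatment 1136 women have to be randomized".

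The variable list in section 8.1 includes: "Conversion from RPCA to epidural analgesia: categorical, quantitative (yes/no)", and the same item for the opposite direction.

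**The concern.** The side effects are defined by being on a drug but are analysed by allocation. Under the stated rule, respiratory depression during rescue RPCA is an epidural-arm event, and hypotension during a rescue epidural is an RPCA-arm event. That is right for comparing strategies. It does not answer how often each drug causes harm in the women who receive it.

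The protocol needs that second answer too. Section 8.1 ends with a decision analysis confined to women who need analgesia, which calls for harm rates in treated women. For pain appreciation, section 8.1 adds a second AUC analysis limited to the time on pain relief. Side effects have no counterpart.

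The per-protocol repeat may not fill the gap. If its population excludes switchers, it could drop women taken off a drug because of a side effect. Sections 1 and 5.2 report such a case: one of 100 women in the pilot and STER data had RPCA stopped for a fall in respiratory rate.

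**Working it through.** **1. The protocol's own figures (section 4.4).** Inputs: difference 1 point (10% of a 10-point scale), SD 2.2, two-sided alpha 0.05, power 90%.
- Per group: 2 × 2.2² × (1.960 + 1.282)² / 1² = 101.7, rounded up to 102.
- Cross-over and non-compliance: 102 / (1 − 0.10 − 0.30)² = 102 / 0.36 = 283.3, rounded up to 284; × 2 = 568.
- Uptake: 568 / 0.5 = 1136.

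All three figures reproduce. The protocol does not print the inflation formula, but its numbers match a factor of 0.6, which treats every departure as a full switch.

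**2. Side effects if all of the 30%/10% switch before exposure to the allocated drug.** Let pR and pE be the risks on RPCA and EA.
- RPCA arm, treated women: 0.7 pR + 0.3 pE.
- EA arm, treated women: 0.9 pE + 0.1 pR.
- Difference: 0.6 (pR − pE).
- With untreated women (50%, same background risk in both arms) in the denominator: 0.5 × 0.6 = 0.3 of pR − pE.

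The protocol gives no side-effect rates, so the rates below are assumptions spanning a range. *Background* is the risk without analgesia. RD is the risk difference in points; RR is the relative risk.

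| pR / pE / background | True RD, RR | Treated women | All randomised |
|---|---|---|---|
| 5% / 0.5% / 0 | 4.5, 10 | 3.65% v 0.95%: 2.7, 3.8 | 1.35, 3.8 |
| 10% / 2% / 0 | 8.0, 5.0 | 7.6% v 2.8%: 4.8, 2.71 | 2.4, 2.71 |
| 20% / 10% / 0 | 10.0, 2.0 | 17% v 11%: 6.0, 1.55 | 3.0, 1.55 |
| 30% / 15% / 5% | 15.0, 2.0 | 25.5% v 16.5%: 9.0, 1.55 | 4.5, 1.42 |

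With no background risk, 50% uptake halves the RD but leaves the RR unchanged. The fall in RR then comes from switching alone.

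**3. Power (two-sided 0.05).** For the last three rows, full adherence with 284 per arm gives 0.98, 0.92 and 0.99. Intention to treat with 568 per arm gives 0.72, 0.51 and 0.62. Intention to treat among treated women, 284 per arm, gives 0.73, 0.54 and 0.75. Without background risk, nearly all the loss comes from switching. Full adherence is a benchmark, not what a by-drug analysis would achieve.

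**4. If switchers start the allocated drug and are then exposed to both (independent risks).** RD among treated women, against the true value:
- 5% / 0.5%: 5.15% v 1.0%, RD 4.15 against 4.5; RR about 5.2 against 10.
- 10% / 2%: 7.6 against 8.0.
- 20% / 10%: 10.6 against 10.0.
- 30% / 15%: 15.6 against 15.0.

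The difference is nearly preserved, but attribution is not. In the first example the EA arm's 1.0% includes 0.1 × 5% = 0.5 points from remifentanil, which is half of that arm's events.

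**5. If the 30%/10% instead receive no analgesic.** For the last three rows of the table, the RD over all randomised women is 0.25 to 0.32 of the true RD, and no harm is counted against the other arm.

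**6. An example that needs no assumed rate.** Post spinal headache (listed under maternal morbidity in section 6.1.2) follows dural puncture at epidural placement (section 5.2). If all 30% of the RPCA arm convert to EA, that arm shows 0.3/1.0 = 30% to 0.3/0.9 = 33% of the EA arm's rate. The range depends on whether EA-arm switchers first had an epidural.

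**The case against.** The strongest reply is that intention to treat fits the question. The trial compares RPCA with EA as first choice, rescue is part of each strategy, and hypotension on a rescue epidural is a real consequence of starting with RPCA. Women who convert are a selected group, so a by-drug comparison loses the protection of randomisation. This stands, and it is why the by-drug analysis should be an addition and not a replacement.

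A second reply is that safety populations and attribution rules usually belong in a statistical analysis plan. Only the protocol was available, and a SAP may contain them. That limits the weight of the point. The protocol nevertheless fixes a general rule with no exception for side effects, so a SAP would have to add to it expressly.

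Four stronger readings are tempting, and the text does not support them:
- *That 30% and 10% are expected to switch drugs.* Section 4.4 combines cross-over with non-compliance, so these are upper limits for switching.
- *That untreated women are in the side-effect denominators.* Section 6.1.2 records side effects only while pain relief is given, and the protocol does not settle the denominator.
- *That events cannot be assigned to a drug.* Section 8.1 is a variable list, not the case report form. It also lists the time from request to start and the duration of analgesia, though not per drug. The AUC over the time on pain relief needs start and stop times, and section 6.3 requires frequent monitoring.
- *That the per-protocol repeat necessarily drops switchers.* Its population is undefined. It may be a partial remedy, but excluding switchers would still not attribute their events to the drug received.

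**Conclusion.** The point holds as a gap, not as an error in the main analysis. The stated analyses, intention to treat and an undefined per-protocol repeat, do not provide side-effect rates by drug received.

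The size depends on what the 30%/10% turn out to be. With full switching before exposure, the risk difference is 0.6 of the drug-to-drug difference among treated women and 0.3 over all randomised; in the assumed examples the relative risk falls from 10 to 3.8, from 5.0 to 2.71, or from 2.0 to between 1.42 and 1.55. With exposure to both drugs, the difference among treated women stays close to the true value and can even widen, and the problem is attribution alone.

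A reader might infer that intention to treat must push the safety comparison towards no difference. The documents do not support that: the direction and size vary with the switching pattern, and all event rates used here are assumptions. This is a cheap improvement.

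**What to change.** 1. In section 8.1, keep intention to treat as the comparison of the two first-choice strategies.
2. Add a prespecified analysis of the maternal side effects in section 6.1.2, in women who received any study analgesic, by the drug being received at onset. Show events after a switch separately.
3. State the denominator for each side-effect analysis, in particular whether women who received no analgesic are counted.
4. Define the per-protocol population and say how women who switch because of a side effect are handled.
5. Make sure the case report form records start, stop and switch times for each drug; the variable list gives conversion only as yes/no.

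The cost is a few sentences of protocol text and, if not already present, two or three time fields. These should be in place before data collection, because switch times not captured may be unrecoverable. The downside is small: the by-drug comparison is not randomised and must be reported as such, beside intention to treat.
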